#### Secondary outcomes

Biomarkers at ages 6 weeks and 3, 6 and 12 months
Plasma marker of chronic inflammation: (AGP; at 6 weeks and 3 and 12 months)Stool biomarker of intestinal inflammation: myeloperoxidaseStool biomarker of intestinal permeability: α1-antitrypsin (AAT)Plasma marker of acute inflammation: C-reactive protein (CRP)Plasma marker of gut mucosal integrity: intestinal fatty acid-binding protein (IFABP)Plasma growth hormones: insulin-like growth factor (IGF)-1 and its carrier protein IGF-binding protein 3Stool pH

Clinical outcomes to age 2 years
MortalityHospital admissionAll-cause sick-child clinic visitsDisease-specific sick-child clinic visits (e.g. diarrhoea; respiratory and skin infections)Anthropometric outcomes: weight, length, mid-upper arm circumference (MUAC), head circumference

Feeding and WASH practices and environmental factors that may influence the development of the gut microbiome will be assessed by questionnaires.

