### Sample size {14}

A total of 600 newborns will be recruited. For the primary outcome, we predict raised AGP (> 1 g/L) in 35% infants at age 6 months in the control group [22]. The study requires a total of 524 infants (131 per am) to demonstrate a 50% reduction (relative risk = 0.50) in the prevalence of the primary outcome from 35% in the control arm to 17.5% in any of the intervention’s arms with 80% power and *α* = 0.0167. The alpha of 0.0167 is required to allow for three comparisons, one for each intervention arm, against the control arm. We will recruit 150 infants per group to allow for 13% dropouts.

We have used AGP concentration as a dichotomous outcome as a conservative approach as we wish to recruit sufficient numbers of children to compare other important biomarkers between groups. Using values of biomarkers as continuous variables will increase the power of the study to detect differences between the study arms. Using AGP as an example, we predict a mean log_10_ value of − 0.24 g/L in controls based on data from Zimbabwe [20]. In total, 102 infants in the intervention and the control group are required to show that mean AGP concentration is 20% lower in the intervention compared with the control group with 90% power at the 5% significance level.

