Analysis of the secondary endpoints with single measurements will also be presented in the ITT and per-protocol (PP) populations and in a similar fashion as for the primary endpoint analysis using generalised linear method. The PP population will be all randomised study subjects who complete 75% or more of the supervised doses. For continuous outcomes, normal distribution and identity link function will be used, from which mean difference together with its 95%CI will be derived. Generalised linear mixed model (GLMMIX) will be employed for the analysis of secondary outcomes with repeated measurements. The GLMMIX model will have treatment, visit, interaction between treatment and visit as fixed effects, baseline measurement of an outcome as covariate, and subject as random effect. The treatment difference between two treatment arms at each visit together with its 95% confidence interval will be derived from the GLMMIX model. Missing data will be treated as missing completely at random in the GLMMIX model analysis and no imputation of primary or secondary endpoints will be made. For the analysis of binary secondary outcomes with repeated measurements, the GLMMIX model will have a binomial distribution and logit link function. The odds ratio between two treatment arms at each visit together with its 95% confidence interval will be derived from the GLMMIX model. For the analysis of continuous secondary outcomes with repeated measurements, the GLMMIX model will have a normal distribution and identify link function. The mean difference between two treatment arms at each visit together with its 95% confidence interval will be derived from the GLMMIX model.

For anthropometric outcomes, *z* scores will be calculated using the WHO Anthro Survey Analyser and WHO 2006 child growth standards [47]. Analyses will include both the comparison of anthropometric indices between intervention groups at different time points and also growth expressed as change in indices over time.

Analyses of the potential adverse effects of the dietary supplements will be done in the safety population.

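### The two planning assumptions for control-arm AGP do not fit together if log10 AGP is roughly normal, so the stated 80% power depends on an unreconciled 35% prevalence

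*Protocol article*

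**What the plan says.** All the planning figures are in the protocol article, Sample size {14}.

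- **Primary outcome.** "we predict raised AGP (> 1 g/L) in 35% infants at age 6 months in the control group [22", citing one source. "The study requires a total of 524 infants (131 per am) to demonstrate a 50% reduction (relative risk = 0.50"), that is, "from 35% in the control arm to 17.5% in any of the intervention’s arms with 80% power" and alpha 0.0167. That alpha is attributed to the three comparisons of an intervention arm with control. Recruitment is 150 per group to allow for 13% dropout.
- **Continuous example.** The next paragraph calls the dichotomy conservative and says that continuous values will increase power. With AGP as its example, it predicts a mean log10 value of −0.24 in controls from Zimbabwean data (a different source). It then says that "102 infants in the intervention and the control group are required to show that mean AGP concentration is 20% lower" in the intervention group, "with 90% power at the 5% significance level". The sentence opens by calling 102 a total, but does not say whether that means each group or both together. It gives no SD and no age for the Zimbabwean figure.

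Elsewhere, Primary outcome and Statistical methods {20a} treat 6-month AGP as above or below 1 g/L. Secondary outcomes lists "Plasma marker of chronic inflammation: (AGP; at 6 weeks and 3 and 12 months"), which leaves out 6 months.

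**The concern.** Both paragraphs offer a prediction for the same biomarker in this trial's control group. A log10 mean of −0.24 is a geometric mean of 0.575 g/L, well below the 1 g/L cut-off. Whether 35% of infants can still lie above the cut-off depends on the spread, and the continuous calculation fixes the spread even though it does not print it.

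The 131 per arm rests wholly on the 35%. If the true control prevalence is much lower, halving it is a small absolute difference, and a null primary result could reflect low prevalence rather than no effect. The document also argues that continuous AGP is more powerful, yet its outcome list contains no continuous AGP at the primary time point.

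**Working it through.** **1. The plan's own primary figure.** Inputs: 35% versus 17.5%, alpha 0.0167 two-sided (z = 2.393), power 80% (z = 0.842), mean proportion 0.2625.

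n = [2.393·√(2·0.2625·0.7375) + 0.842·√(0.35·0.65 + 0.175·0.825)]² / 0.175² = 130.9, so 131 per arm, with power 80.0%. The figure reproduces; any difficulty lies in its input.

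**2. The SD implied by the continuous example.** A 20% lower mean is −log10(0.8) = 0.0969. From n per group = 2·[SD·(1.960 + 1.282)/0.0969]²:

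SD = 0.0969·√(n/2)/3.242

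- 102 per group: 0.0969·√51/3.242 = 0.2135
- 102 in total (51 per group): 0.0969·√25.5/3.242 = 0.151

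**3. The prevalence that follows, with log10 AGP approximately normal.** P(AGP > 1 g/L) = 1 − Φ(0.24/SD).

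| Reading of 102 | SD | 0.24/SD | Share above 1 g/L |
|---|---|---|---|
| Per group, two-sided | 0.2135 | 1.124 | 13.0% |
| Total, two-sided | 0.151 | 1.590 | 5.6% |

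A one-sided 5% test would give 15.5% and 7.6%. None of these is near 35%.

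**4. In reverse.** For 35% above 1 g/L with mean −0.24, SD = 0.24/0.3853 = 0.623. The 20% difference then needs 2·(0.623·3.242/0.0969)² ≈ 868 per group, not 102. If instead SD is 0.2135, 35% needs a geometric mean of 10^(−0.2135·0.3853) = 0.83 g/L, not 0.575.

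**5. Primary power for a halving at alpha 0.0167** (same formula as step 1).

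| Control prevalence | Power, 131 per arm |
|---|---|
| 35% | 80% |
| 30% | 70% |
| 25% | 58% |
| 20% | 45% |
| 13% | 27% |
| 5.6% | 10% |

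With all 150 per arm analysed, power at 13% is still only 31%.

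**6. Continuous log10 AGP at alpha 0.0167, 20% lower mean.** Power = Φ(0.0969/(SD·√(2/n)) − 2.393).

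- SD 0.2135: 102 per group gives 80%; 131 per group gives 90%.
- SD 0.151: 131 per group gives more than 99%.

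**7. The same 20% shift seen through the 1 g/L cut-off** (SD 0.2135, 131 per arm, alpha 0.0167).

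- Control 13.0%: treated share 1 − Φ((0.24 + 0.0969)/0.2135) = 5.7%; power 36%.
- Control 35% (mean −0.0823): treated share 1 − Φ((0.0823 + 0.0969)/0.2135) = 20.1%; power 62%.

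**The case against.** The strongest defence is that the two predictions come from different sources, that the Zimbabwean figure is an illustration of undisclosed age, and that its SD is inferred here. All of this stands. A reader might infer that the two figures cannot both describe the control arm. That is too strong: with no distributional assumption, the one-sided Chebyshev (Cantelli) bound at SD 0.2135 allows up to 0.2135²/(0.2135² + 0.24²) = 44% above the cut-off. On the total reading the bound is 28%. The conflict therefore needs approximate normality on the per-group reading. A reader might also infer that 35% is wrong and the trial underpowered; nothing in the document shows that.

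On alpha, 0.0167 is stated only for the primary comparisons. Quoting the continuous example at 5% breaks no stated rule.

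It is also tempting to read "the GLMMIX model will have a normal distribution and identify link function" as fixing continuous outcomes on the untransformed scale. It does not: that is equally the model for log10 values, and a statistical analysis plan that is not shown may specify the transformation. That plan may also add a 6-month log10 analysis. What remains is that the protocol's explicit list of AGP time points omits 6 months while its sample-size argument relies on continuous AGP for greater power.

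**Conclusion.** The point holds in conditional form. If log10 AGP is approximately normal, the continuous example implies about 13% of controls above 1 g/L (102 per group) or about 6% (102 in total), against the 35% used to size the trial. The arithmetic behind 131 per arm is correct, but its 80% power is secured only if the 35% is right. Across the range that the document's own inputs span, power for a halving runs from 80% down to 27% or 10%. The document gives no basis for choosing between the inputs. The per-group and total readings also differ materially, so the power figures for continuous AGP depend on which was meant.

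**What to change.** 1. State the SD and the age behind the −0.24, and whether 102 is per group or the total of both groups. Reconcile these with the 35%.
2. Report primary power for a halving over control prevalence of about 6–35%, in place of the single figure.
3. If the continuous figure is meant to support the three arm-versus-control comparisons, give it at 0.0167 as well. If 102 is per group, that number has 80% power and 131 per arm has 90%.
4. Keep the sample size and the > 1 g/L primary outcome. Pre-specify log10 AGP at 6 months as a supportive analysis of the primary objective, reported as a geometric mean ratio. With SD 0.2135 it has 90% power for a 20% lower AGP at 131 per arm and 0.0167, against 36–62% for the dichotomised outcome.

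The cost is some wording, one extra regression and a less favourable statement of power. The gain is that a null primary result could be read against both the observed prevalence and a more sensitive analysis fixed in advance.

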### Recruitment {15}

Recruitment of 600 newborns is expected to require 12 months with a recruitment rate of approximately 50 newborns per month at the Homa Bay hospital. We plan to pace recruitment by including approximately 12 eligible infants/week to ensure adequate staff and transport are available to complete subsequent follow-up visits. We will recruit infants consecutively according to eligibility but pause recruitment once the target number of infants for that day/week has been reached.

## Assignment of interventions: allocation

### Sequence generation {16a}

The trial statistician at LSTM, UK, will prepare computer-generated random allocation sequences using blocks of random size and stratified according to HIV exposure. The allocation ratio will be 1:1:1:1.

### Concealment mechanism {16b}

The randomisation sequences will use dummy codes (e.g. A, B, C and D). The random sequences will be held by the independent statistician and the trial pharmacist and concealed from all other members of the research team. Another independent statistician who is not involved in the study will assign the dummy codes to each of the four study arms.

### Implementation {16c}

The allocation sequences will be forwarded to the trial pharmacist based in Kenya who will prepare sequentially numbered, sealed, opaque envelopes each with a unique study number according to the random allocation sequences. The envelope will contain a card indicating the intervention group and colour coded to match the supplement capsules. These opaque envelopes will be opened sequentially upon enrolment of each newborn in the presence of the mother/carer and research staff.

## Assignment of interventions: Blinding

### Who will be blinded {17a}

Staff allocating newborns to the study arms and laboratory staff doing the assays for the primary and secondary outcomes will be blinded to the allocation sequence. The trial statistician will also be blinded regarding the treatment code when developing the statistical analysis plan and writing the statistical programmes, which will be validated and completed using dummy randomisation codes. The allocation sequence will only be provided to the study team after locking of the database for the primary outcome, and after the statistical analysis plan has been signed off by the Chief Investigator, the trial statistician and a representative of the independent Data Monitoring and Ethics Committee (DMEC).

### Procedure for unblinding if needed {17b}

This is not required in this open study.

## Data collection and management

### Plans for assessment and collection of outcomes {18a}

Biomarkers of gut health and growth will be measured in capillary blood samples (up to 1 ml) collected during visits to the research clinic and stool samples collected from homes at 6 weeks, 3 months, 6 months and 12 months. The stool samples obtained from homes will be collected by the mother/carer who will have been provided with materials to obtain a late evening or early morning stool prior to going to the facility for the scheduled visit. The materials provided include a disposable nappy or plastic sheet, pre-labelled (with participant ID, date and visit) sample container with a scoop, plastic specimen bag, small cold box with 3 frozen ice packs with a biohazard label, a bar of soap, gloves, tissue paper, biohazard bag and ziplock bags. The mother/carer is asked to collect stool from the nappy or plastic sheet until 2 ml if the usual consistency is liquid or semi-formed or the size of two marbles if formed. Study staff prior to stool collection will inquire if the child had diarrhoea (described as three or more loose stools in 24 h) in which case stool collection will be suspended until the episode has subsided. The sample will be delivered to the lab within 12 h from the time the icepacks are packed into cooler box. The time from sample collection to receipt in the laboratory will be recorded.

In plasma, AGP (Human alpha 1-Acid Glycoprotein Quantikine ELISA), CRP (Human C-reactive protein/CRP quantikine ELISA) and IFABP (Human FABP2/IFABP Quantikine ELISA), IGF-1 and IGFBP3 (Human IGF-I and IGFBP-3 Quantikine ELISA) in kits provided by fbio-techne.com, Abingdon, UK. In stool, myeloperoxidase (Human Myeloperoxidase Quantikine ELISA; fbio-techne.com, Abingdon, UK) and AAT (Immunodiagnostik AG; Hamburg, Germany) will be measured. Kits from other manufacturers may also be considered. For stool pH, an aliquot of stool will be diluted 1:10 in sterile water, mixed with a vortex mixer for 4 min, centrifuged to precipitate solids (2 min, 12,000 relative centrifugal force) and pH measured in the supernatant using a pH metre [46].

Laboratory assays will be carried out according to the manufacturer’s instructions. All assays will be carried out in duplicate and repeated should there be a discrepancy in values. Processing, analysis and storage of samples will be undertaken at the Research Laboratories at the Kenya Medical Research Institute (KEMRI) Centre for Global Health Research, Kisumu, Kenya.

Clinical outcomes will be assessed as follows:
Mortality and hospital admissions will be recorded by a questionnaire applied during each scheduled and unscheduled visit and information copied from any health cards carried by the mother/carer and/or from hospital records and reported as serious adverse events (SAEs).Episodes of all-cause and disease-specific sick-child clinic visits will be recorded during each scheduled visit as reported by the mother/carer and information copied from any health cards carried by the mother/carer and/or from clinic records.Weight will be measured to the nearest 100 g using electronic scales. MUAC will be measured at the mid-point between the tip of the shoulder and the tip of the elbow using a non-stretchable MUAC tape to the nearest 0.1 cm. Length will be measured to the nearest 0.1 cm using a length board. Head circumference will be measured to the nearest 0.1 cm using a non-stretchable tape measure. All measurements will be performed in duplicate and a third measurement made should values disagree by a pre-specified amount. Scales and length boards will be checked daily for accuracy using a standard weight and a ruler.

### Plans to promote participant retention and complete follow-up {18b}

Several community sensitisation meetings were held in Homa Bay town sub-county and approximately 5 km radius before the start of the study to provide information and hear and respond to questions or concerns raised regarding the study. These meetings will continue during the study as forums to raise and address any concerns. During screening, women will be asked whether they live in the catchment area and are willing to adhere to the study protocol including being available for follow-up visits. Detailed directions to participants’ homes as well as contact information, including mobile phone numbers, will be recorded at enrolment. If mothers/carers are not available or present at scheduled follow-up visits, the study team will call them to reschedule the visit or ask them to come to the research clinic at Homa Bay Hospital for evaluation, offering transport reimbursement. Subjects judged to be non-compliant may continue in the study with frequent checks on participant well-being by the study team to address study-related concerns, prevent misinformation from arising and allow continuity with study procedures. Mothers/carers will be provided with a mobile phone number for members of the research team to facilitate communication.

### Data management {19}

Data will be collected on case report forms (CRFs) and questionnaires in paper format. The quality of data collection and data entry will be maximised through training of field staff in standardised methodology and by range and missing data checks during the study. Field staff will be required to demonstrate competence before conducting fieldwork. Forms using HP Teleform software will be designed for semi-automated transcribing of data into an electronic database using scanning and Optical Character Recognition, intelligent document recognition and data validation using checksum algorithms, cross-field validation, range and consistency checks. Verification of information against source documents will also be undertaken by data managers. Once validated, the data will be transferred to the target database along with a PDF of the original image of the CRFs, to generate an electronic copy of all paper-based documents.

Verified and validated data will be stored via the cloud on a secure, highly fault-tolerant, storage area network servers at KEMRI in Kisumu and at LSTM in Liverpool. Data will be backed up in Kenya on a continuous basis on a secure off-site server and on encrypted standalone hard drives. Once the data validation phase is completed by the Data Manager at LSTM, the database will be locked and transferred for statistical analysis at LSTM including further consistency checks and data cleaning (e.g. in Stata). The final cleaned database will be available as SAS, STATA and in SPSS format, with an embedded data dictionary.

The full study protocol, supporting documents and the fully anonymised, individual participant-level database will be made publicly available once the study findings have been published. The Data Manager will produce a document summarising the methods used to generate the data with a full description of all procedures, analyses, data capture tools, coding and description of variables which will be published alongside the research database.

The research data will be stored long term in the original electronic format, in a unified database and a public database that contains all research data other than participant identifiable data. The anonymised data will be preserved for at least 10 years.

### Confidentiality {27}

All information regarding the participants will remain confidential to the extent allowed by law. Unique numerical identifiers will be used for data entry. All screening forms and CRFs will be kept in a secured location with access limited to authorised study staff. Unique numerical identifiers will be used for the computer-based data entry and stool and blood samples. Publications will contain only aggregated data; no identifying information will be included to ensure individual patient anonymisation of all data and results made public.

### Plans for collection, laboratory evaluation and storage of biological specimens for genetic or molecular analysis in this trial/future use {33}

Any remaining stool and blood samples will be stored long term for possible future analyses relevant to gut health and nutrition in early life. These may include nutrient assays in blood (e.g. iron), detection of the probiotic organisms and specific enteropathogens in stool and microbiome analysis. Shipment of the minimum aliquots of stool or serum for analysis in the UK would only be undertaken following approval from the relevant authorities.

## Statistical methods

### Statistical methods for primary and secondary outcomes {20a}

Demographic, clinical and laboratory data and also variables reflecting feeding, WASH practices and environmental factors will be summarised using simple descriptive statistics. Continuous variables will be summarised according to the number of subjects with non-missing data as mean, standard deviation, median, minimum and maximum. Categorical variables will be summarised according to the absolute frequency and percentage of subjects in each category level. The denominator for the percentages is the number of subjects with data available unless noted otherwise.

The primary outcome analysis will be based on the intention-to-treat (ITT) population which will include all randomised study subjects. The proportion of infants aged 6 months with abnormal AGP concentration (> 1 g/L) in each intervention arm will be compared with the proportion in the control arm. Data will be analysed using generalised linear models with treatment as the only predictor, AGP concentration at baseline as covariate, binomial distribution and log link function, generating the estimates of treatment effects in relative risk and their 95% confidence intervals (CI). Covariate-adjusted analysis will also be performed with covariates that affect the primary outcome (e.g. season of birth, HIV exposure, mode of delivery, mode of feeding, exposure to antibiotics, WASH and environmental factors such as water source, sanitation facilities, hygiene practices, use of soap, number of siblings, proximity to animals). Subgroup analysis will also be performed on the covariates used in the covariate-adjusted analysis.

Analysis of the secondary endpoints with single measurements will also be presented in the ITT and per-protocol (PP) populations and in a similar fashion as for the primary endpoint analysis using generalised linear method. The PP population will be all randomised study subjects who complete 75% or more of the supervised doses. For continuous outcomes, normal distribution and identity link function will be used, from which mean difference together with its 95%CI will be derived. Generalised linear mixed model (GLMMIX) will be employed for the analysis of secondary outcomes with repeated measurements. The GLMMIX model will have treatment, visit, interaction between treatment and visit as fixed effects, baseline measurement of an outcome as covariate, and subject as random effect. The treatment difference between two treatment arms at each visit together with its 95% confidence interval will be derived from the GLMMIX model. Missing data will be treated as missing completely at random in the GLMMIX model analysis and no imputation of primary or secondary endpoints will be made. For the analysis of binary secondary outcomes with repeated measurements, the GLMMIX model will have a binomial distribution and logit link function. The odds ratio between two treatment arms at each visit together with its 95% confidence interval will be derived from the GLMMIX model. For the analysis of continuous secondary outcomes with repeated measurements, the GLMMIX model will have a normal distribution and identify link function. The mean difference between two treatment arms at each visit together with its 95% confidence interval will be derived from the GLMMIX model.

For anthropometric outcomes, *z* scores will be calculated using the WHO Anthro Survey Analyser and WHO 2006 child growth standards [47]. Analyses will include both the comparison of anthropometric indices between intervention groups at different time points and also growth expressed as change in indices over time.

Analyses of the potential adverse effects of the dietary supplements will be done in the safety population.

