### Outcomes {12}

#### Primary outcome

The primary outcome will be raised plasma AGP concentration (> 1 g/L) at age 6 months as a key biomarker of poor gut health contributing to chronic systemic inflammation and impaired growth.

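### Randomisation is stratified by HIV exposure, but the primary model (treatment plus baseline AGP) and the mixed models omit the stratum: the intervals are valid but slightly wide, and a little power is lost

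*Protocol article*

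**What the plan says.** Under Sequence generation {16a}, the trial statistician prepares "computer-generated random allocation sequences using blocks of random size and stratified according to HIV exposure", and "The allocation ratio will be 1:1:1:1". HIV exposure is the only stratification factor named.

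Under Primary outcome, the endpoint is binary: "The primary outcome will be raised plasma AGP concentration (> 1 g/L) at age 6 months".

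Under Statistical methods {20a}, the sentence on the primary comparison opens "Data will be analysed using generalised linear models with treatment as the only predictor". With its remaining terms, it specifies "generalised linear models with treatment as the only predictor, AGP concentration at baseline as covariate, binomial distribution and log link function". Read as a whole, the sentence gives two terms, treatment and baseline AGP, and no HIV term. The next step is separate: "Covariate-adjusted analysis will also be performed with covariates that affect the primary outcome (e.g. season of birth, HIV exposure, mode of delivery", followed by a longer list of examples. Subgroup analyses use the same covariates, and the section on additional analyses {20b} names HIV-exposed infants as a subgroup.

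For repeated secondary outcomes, the same section says "The GLMMIX model will have treatment, visit, interaction between treatment and visit as fixed effects", adding the baseline measurement as covariate and subject as random effect. HIV exposure is again absent.

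**The concern.** Stratified blocks keep HIV-exposed infants evenly spread over the arms. If exposure predicts the outcome, that removes one source of chance difference between arms, so the estimated relative risk varies less from trial to trial than under simple randomisation. A model without the stratum does not know this. It still counts the between-stratum variation as error, reports a standard error that is too large, and tests below its nominal level.

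The plan itself gives grounds to expect some association, since it lists HIV exposure among factors that affect the primary outcome. It also notes, in the details of the supplements, that exposed infants take daily co-trimoxazole from age 4–6 weeks, although it states no direction of effect on AGP. At stake is a modest amount of power on the primary comparison, and agreement between the design and its analysis.

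**Working it through.** **Inputs from the protocol article** (Sample size {14}): control risk 35%, intervention risk 17.5%, α = 0.0167 per comparison, 80% power, 131 evaluable per arm.

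**Assumed inputs** (not in the documents): share exposed π = 10–30%; relative risk of raised AGP in exposed versus unexposed r = 1.5–2.5, the same in both arms. Baseline AGP is ignored.

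**Step 1. The plan's own sample size.** Two-sided, pooled variance, no continuity correction, with mean risk 0.2625:

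n = [2.393·√(2 × 0.2625 × 0.7375) + 0.842·√(0.35 × 0.65 + 0.175 × 0.825)]² / 0.175² = 130.9, so 131 per arm and 524 in total. This reproduces. Allowing for dropout, 131/0.87 = 150.6, against the stated 150.

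**Step 2. Variance the unadjusted model reports.**

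V_un = (1 − p₁)/(n·p₁) + (1 − p₀)/(n·p₀)

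At the design effect: 0.825/(131 × 0.175) + 0.65/(131 × 0.35) = 0.03599 + 0.01418 = 0.05016, so SE = 0.2240. Under the null (35% in both arms): 2 × 0.01418 = 0.02835, so SE = 0.1684.

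**Step 3. True variance under stratified, balanced allocation.** The between-stratum part drops out of each arm:

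V_true = V_un − 2c/n, where c = π(1 − π)(r − 1)² / [1 + π(r − 1)]²

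Worked example, π = 0.2 and r = 2: c = 0.16/1.44 = 0.1111; 2c/131 = 0.00170; V_true = 0.04847; SE = 0.2202. The interval is 0.2240/0.2202 − 1 = 1.7% too wide.

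**Step 4. Results at the design effect.** The adjusted SE comes from the Fisher information of a log-binomial model with treatment and HIV exposure. Power uses a Wald test of log RR = log 0.5 at α = 0.0167. The loss is measured against the power the unadjusted test actually has under stratified allocation.

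| π, r | True SE | V_true/V_un | Too wide vs true SE | Adjusted SE | Wider than adjusted model | Power lost vs true SE / adjusted model (points) |
|---|---|---|---|---|---|---|
| any, 1.0 | 0.2240 | 1.000 | 0% | 0.2240 | 0% | 0 / 0 |
| 10%, 1.5 | 0.2233 | 0.994 | 0.3% | 0.2230 | 0.5% | 0.2 / 0.4 |
| 20%, 2.0 | 0.2202 | 0.966 | 1.7% | 0.2183 | 2.6% | 1.3 / 2.1 |
| 30%, 2.5 | 0.2162 | 0.932 | 3.6% | 0.2131 | 5.1% | 2.6 / 3.9 |

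The largest excess over the adjusted model within these ranges is 5.4% (π = 20%, r = 2.5), with 4.1 points of power. The Wald test on log RR has about 76% power before adjustment. It is a different statistic from the difference in proportions behind the 80%, so only the change matters here.

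**Step 5. Under the null.** V_true/V_un is 0.989, 0.940 and 0.879 for the three non-null rows. True size at nominal 5% is 2·[1 − Φ(1.96/√ratio)] = 4.9%, 4.3% and 3.7%.

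**Step 6. Simulation check.** 8,000 trials per setting, random blocks of 4 or 8 within strata, unadjusted versus Mantel-Haenszel RR. At the design effect the ratio of mean unadjusted to mean stratified SE was 1.000 (no association), 1.005 (20%, r = 1.5), 1.017 (20%, r = 2) and 1.019 (30%, r = 2). Under the null the corresponding figures were 1.000, 1.009, 1.031 and 1.035. At r = 2, non-coverage of the 95% interval was 4.1–4.5% unadjusted and 4.5–5.3% stratified. The two estimators had almost the same empirical spread. Stratification has already delivered the precision, and the unadjusted model fails to report it.

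No figure was computed for the repeated-measures models. The omission there is the same in kind.

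**The case against.** **The association is assumed.** This stands. The article gives no prevalence and no effect on AGP, and HIV exposure is one of about a dozen example covariates. With r of 1.25–1.5 and up to 30% exposed, the interval at the design effect is at most 0.8% wider than the adjusted one. With no association nothing is lost.

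**Baseline AGP is already in the model.** Also true. A reader who stops at the words about the only predictor might infer a model with treatment alone, but the same sentence adds the covariate. Any overlap between baseline AGP and HIV exposure would shrink the figures above. The stratum is still absent.

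**An HIV-adjusted estimate is planned.** It is, but as one item in an open list in an additional analysis, so the primary interval remains the one that ignores the stratum.

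**The analysis plan may settle it.** It may, but the article does more than leave the model open: it lists the terms of both models and leaves this one out.

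**Stronger readings that do not hold.** A reader might take the null variance ratio of 0.879 as a loss of 12% of the sample, or 18 of 150 infants per arm. Power is lost under the alternative, where the same extreme setting gives a ratio of 0.932, about 7% or 10 infants per arm, against the true standard error. A reader might also infer inflated type I error, but the error runs the other way. Nor is this a confirmatory comparison at risk: under Trial design {8} the article calls the trial exploratory.

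**Conclusion.** The point holds as a small matter of efficiency and consistency. The stratification factor is missing from the primary and repeated-measures models, although the plan treats it as prognostic. The primary intervals stay valid and err on the wide side. Under the assumed 10–30% exposed and prognostic relative risk of 1.5–2.5, the cost at the design effect is about 0.3% to 3.6% of interval width against the true standard error, or about 0.5% to 5% against an adjusted log-binomial model, and about 0.2 to 4 points of power. Confidence is high in the omission and its direction. It is low in the size, which rests on two inputs the documents do not give and could be zero.

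**What to change.** Add HIV exposure (exposed or unexposed) as a fixed term in the primary model beside treatment and baseline AGP, and in every mixed model. Name a fallback in advance in case the log-binomial model does not converge: a standardised relative risk, or modified Poisson regression with robust standard errors. Keep the relative risk without the HIV term as a supportive figure. Settle this before the allocation is released.

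The variable is already recorded for randomisation, so no new data are needed, and the sample size stands because it is an unadjusted two-proportion calculation. There are two small costs. An extra term can add to convergence problems under the log link, hence the fallback. In the binary mixed models with a logit link, the odds ratio becomes conditional on HIV exposure, and the report should say so. A plain Mantel-Haenszel relative risk would respect the stratification but does not directly accommodate the continuous baseline AGP, so it suits a check better than the primary estimate.
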